## Abstract

**Background:**

Infants born at extreme prematurity (below 28 weeks' gestation) are at high risk of developmental disability. A major risk factor for disability is having a low level of thyroid hormone which is recognised to be a frequent phenomenon in these infants. At present it is unclear whether low levels of thyroid hormone are a cause of disability, or a consequence of concurrent adversity.

**Methods:**

We propose an explanatory multi-centre double blind randomised controlled trial of thyroid hormone supplementation in babies born below 28 weeks' gestation. All infants will receive either levothyroxine or placebo until 32 weeks' corrected gestational age. The primary outcome will be brain growth. This will be assessed by the width of the sub-arachnoid space measured using cranial ultrasound and head circumference at 36 weeks' corrected gestational. The secondary outcomes will be (a) thyroid hormone concentrations measured at increasing postnatal age, (b) status of the hypothalamic pituitary axis, (c) auxological data between birth and 36 weeks' corrected gestational age, (d) thyroid gland volume, (e) volumes of brain structures (measured by magnetic resonance imaging), (f) determination of the extent of myelination and white matter integrity (measured by diffusion weighted MRI) and brain vessel morphology (measured by magnetic resonance angiography) at expected date of delivery and (g) markers of morbidity including duration of mechanical ventilation and chronic lung disease.

We will also examine how activity of the hypothalamic-pituitary-adrenal axis modulates the effects of thyroid supplementation. This will contribute to decisions about which confounding variables to assess in large-scale studies.

**Trial registration:**

Current Controlled Trials ISRCTN89493983

## Background

In the immediate postnatal period of babies born at term, hypothyroidism causes neurodevelopmental disability[1,2]. This disability can be prevented by giving supplementary thyroid hormone[3,4]. Infants born at extreme prematurity (i.e. before 28 weeks' gestation) are at high risk of neurodevelopmental disability, particularly if they are hypothyroid [4-6]. Some, but not all, forms of thyroid supplementation appear to reduce the incidence of poor neurodevelopmental outcome in infants born at extreme prematurity [7-9].

### Hypothyroidism in early infancy causes neurodevelopmental disability which can be prevented by giving supplementary thyroid hormone

In congenital hypothyroidism (CH) early treatment with thyroid replacement reduces severe developmental deficits[1]. Even mild thyroid hormone insufficiency can produce measurable, but preventable, deficits in neuropsychological functions[3,4]. Magnetic resonance imaging (MRI) and spectroscopy (MRS) have documented brain metabolic changes in untreated CH. The reversal of these abnormalities following replacement therapy is thought to be due to improved myelination[10]. This suggests an important role for thyroid hormone in the developing brain in the early postnatal period.

### Infants born before 28 weeks of gestation are at high risk of disability

Advances in neonatal medicine have resulted in an increase in survival of preterm infants below 28 weeks' gestation. Infants born extremely prematurely at this low gestation are at particular risk of neurological abnormalities [11-13]. The normal development of the brains of these infants is at high risk of disruption with consequent acquired damage especially to the white matter because of multiple factors[14]. These are thought to include hypoxic ischaemia, free radical injury because of low concentrations of antioxidants, undernutrition and sepsis[15]. This period in brain development is important because neuronal migration has only just finished (at about 20 weeks) and synaptogenesis is occurring and therefore the cellular milieu is critical[16].

Brain MRI studies of survivors of low birth weight, who have subtle cognitive abnormalities have been shown to have diminished volumes of the caudate nucleus and hippocampus and these findings have been correlated with lower IQ, learning disorder and attention deficit[17,18]. Recent brain MRI studies of preterm infants also show that quantitative cerebral structural abnormalities are related to the degree of immaturity at birth and are followed by abnormal neurodevelopmental outcome[14,19]. Preterm infants assessed at term show reduced myelination when compared to infants born at term[14].

### Evidence of hypothyroidism is common among infants born before 28 weeks of gestation and is associated with an increased risk of disability

Transient hypothyroxinaemia of prematurity as characterised by low blood thyroxine (T4) concentrations with normal or mildly elevated plasma thyroid stimulating hormone (TSH) concentrations is common in infants under 30 weeks' gestation at birth, occurring in up to 69%[9,20-23]. The proportion of preterm infants having hypothyroxinaemia increases with decreasing gestational age[22,24]. A recent large collaborative Scottish study has shown that an extremely premature group of infants of 23–27 weeks' gestation appeared distinctive and were hypothyroxinaemic relative to other groups[20]. The postnatal surge of T4 concentrations described in the term infants was less marked in infants of 31–34 weeks gestation, absent in infants of 28–30 weeks and reversed in infants of 23–27 weeks who had low plasma T4 concentrations.

Low blood thyroid hormone concentrations in the first few weeks of life in preterm infants have been linked with poor neurodevelopment[5,6]. Reuss et al[25] (n = 463) found a 4-fold increased risk of disabling cerebral palsy at 2 years of age associated with hypothyroxinaemia in infants born below 33 weeks' gestation. Den Ouden et al[26] (n = 563) found a higher incidence of neurologic dysfunction at 5 and 9 years of age in association with lower thyroxine concentrations even after adjustments for other perinatal factors in preterm infants born below 32 weeks'. Paul et al[27] found increased mortality and increased incidence of intraventricular haemorrhage in preterm infants with abnormal thyroid function, whilst Leviton et al[26] reported white matter changes predictive of abnormal neurological outcome on cranial ultrasound of neonates with low T4 blood concentrations. In addition, published data have documented a relationship between maternal thyroid deficiency during pregnancy and problems with neuropsychological development of the offspring[28]. However, the questions of whether this hypothyroidism reflects the adversity leading to brain injury, or whether hypothyroidism is a preventable cause of brain injury can only be answered by randomised controlled clinical trials.

### Thyroid supplementation to extreme preterm infants may reduce the risk of disability

A randomised controlled trial of T4 supplementation by Van Wassanaer et al[8,21] showed an improved Bayley Mental Development Index (MDI) and Psychomotor Development Index (PDI) at 2 years among infants born at extreme prematurity who had received T4 supplementation. However, the babies who appeared to benefit were not the primary target population in this study and the positive result was only evident after subgroup analysis. In the whole sample there was no benefit to long term outcome. The reliability of that trial was limited by a small sample size. In other studies, thyroid hormone replacement has been given to preterm infants with either beneficial effects or no apparent effects[7,9,21,29,30]. However, the studies which have been done are of small sample size and have not shown rigorous proof of efficacy of such a treatment.

### Previous studies of thyroid replacement therapy in preterm infants

A Cochrane review of thyroid hormone supplementation in premature infants found that none of the available trials provide good evidence for the value of thyroid hormone supplementation in preterm infants[31]. The results of the meta-analysis found no significant difference in overall mortality. Meta-analysis of two studies[7,8] found no significant difference in Bayley MDI or PDI performed at 7–12 months, death or IQ score at 5.7 years of age. All studies were of small size with the largest by van Wassanaer[8], which enrolled 200 infants under 30 weeks' gestation. However, the sample size for this post hoc subgroup analysis of infants with gestational age below 27 weeks who benefited from the intervention was small comprising just 46 infants (19 in the treatment arm and 27 in the placebo arm). The review concluded that future trials of sufficient size needed to be undertaken to detect the clinically important differences in neurodevelopmental outcome, particularly enrolling the infants most likely to benefit from thyroid hormone therapy such as extremely preterm infants.

The conclusion from these results is that there is biologically plausible evidence that T4 supplementation for very immature babies may improve their neurological outcome, but that more mature babies are not likely to benefit from this intervention. Studies of triiodothyronine (T3) supplementation[22,30] have not provided evidence for improved outcome. Animal studies have shown that the postnatal development of brain structures in rats was entirely dependent on local generation of T3 from T4 by type 2 iodothyronine deiodinase[32,33]. This suggests that normal neurodevelopment requires appropriate T4 supplementation and not T3 supplementation. T3 supplementation appeared to raise plasma free T3 and total T3 concentrations but suppress T4 concentrations[34,35]. T4 supplementation has been shown to suppress T3 concentrations but raise total and free T4 concentrations (FT4)[7,8]. Van Wassanaer et al examined different T4 dosage schemes and concluded that 8 mcg/kg birthweight/day increased T4 and FT4 concentrations most appropriately and prevented transient hypothyroxinaemia during the 6 weeks' treatment[35]. Van Wassanaer also showed that high longitudinal FT4 concentrations were not associated with worse outcome, while low FT4 concentrations were associated with worse neurodevelopmental outcome at 2 and 5 years of age[35]. In the light of these findings, a trial of T4 supplementation is a strong candidate for intervention.

An important practical issue for intervention studies is the need to classify the thyroid status of individual infants. The blood concentrations used in this classification will determine recruitment to the study and the response to monitoring during the intervention. At present, it remains unclear what cut-off point for T4 or FT4 concentrations constitutes hyperthyroxinaemia or hypothyroxinaemia in these preterm infants, particularly in the weeks just after birth. Normative values for thyroid hormones in cord blood for each gestational age have been published[20,24]. It has been suggested that these values can provide normative values in the postnatal period by relating concentrations at a particular corrected gestational age to those of infants born at the same gestational age[20]. However, the implications of this strategy have not been explored in treated infants. We will be able to model the implications of this strategy using the results of this trial.

### The associations of transient hypothyroidism have not been studied among infants born at extreme prematurity

Following birth, thyroid status changes and these changes are influenced by gestational age at birth. The consequences of these changes have not been reported. Longitudinal measures of thyroid status and neonatal progress will be made during this trial and will allow us to describe how thyroid status in the weeks after birth at extreme prematurity is related to neonatal course.

### Thyroid status may affect other organ systems in ways that affect the design of future trials

Thyroid hormones alter metabolic rate[2,28]. Nutritional and growth implications of hypothyroidism have not been studied. Thyroid supplementation could increase nutritional requirements and reduce extrauterine growth. To date, there is little evidence of this occurring among infants born at extreme prematurity. Given that neurodevelopmental outcome may be confounded by the social environment after discharge[13,36], it will be important to include neuroradiological markers of brain development as an intermediate outcome. However, although thyroid hormones are involved in brain development, particularly in myelination[10,37,38], there is a paucity of published data concerning the relationship between thyroid hormone status and brain development in preterm infants. The lack of information about how thyroid status relates to brain size and body growth will hinder clinical trials of thyroid supplementation.

### Other factors may be relevant to the effects of thyroid supplementation on outcome

Factors which may contribute to abnormal thyroid function in very preterm infants include: immaturity of the thyroid gland, immaturity of the hypothalamic-pituitary-thyroid axis, disruption of maternal transfer of T4 through the placenta, relative immaturity of type 1 deiodothyronine monodeiodinase enzyme systems and reduction in thyroid binding globulin (TBG) due to hepatic immaturity[2,23]. Iodine is required for renewal of intra-thyroidal T4, but the concentrations of iodine in the thyroid gland of preterm infants are low[39,40]. This appears to be related to maternal iodine status and effect of inadequate iodine supplementation in parenteral nutrition for preterm infants [39-41].

Abnormal thyroid size is often found in disease states, e.g. goitre[2]. Thyroid size may therefore be a useful marker of thyroid status. However, the only normative study of thyroid size in term infants was limited to 100 infants and did not examine infants born at extreme prematurity[42].

Blood cortisol concentrations decrease as blood T4 concentrations increase with advancing gestational age[34,43]. These observations suggest that there may be an interaction between the cortisol and thyroid systems in preterm infants. Since both hormones have been implicated in early brain development[44,45], this interaction could contribute to the poor neurological outcome of infants born extremely premature. Activity of the hypothalamic-pituitary-adrenal (HPA) axis is central to normal fetal development and neonatal transition[46,47]. Extremely premature infants have low basal blood cortisol concentrations and inadequate stimulated cortisol responses to adrenocorticotrophic hormone in the early neonatal period[44,47]. Cortisol is important for survival during illness and cortisol concentrations are expected to increase during significant stress. In ill adults with low baseline and stimulated cortisol concentrations, mortality is higher[44]. In the preterm infant population, the physiological significance of lower blood cortisol values remains unclear[46,47]. Most studies have not consistently correlated blood cortisol concentrations to physiological markers of cortisol effect and outcome in preterm infants. In a recent study, the HPA axis was found to be unresponsive to standard stimulation tests until 11 days of age in preterm baboons indicating HPA axis immaturity[48]. Activation of the HPA axis and increased blood cortisol concentrations may be essential to respond to the many stressors of extra-uterine existence in the extreme preterm infants. This transient inability of the adrenals to maintain cortisol homoeostasis in premature newborns in the immediate postnatal period has been described as transient adrenocortical insufficiency of prematurity[44].

Valerio et al[30] looked at the effect of thyroid hormone supplementation on blood cortisol concentrations in babies born below 28 weeks GA. The sample size was small with only 31 patients. No significant difference was noted in cortisol concentrations and mortality between the groups. The results of the study suggest that hypothyroxinaemia was not involved in the development of hypocortisolism in preterm infants. However, the medium-term effects of the relationships between these two endocrine systems have not been studied. Further understanding of their roles in the outcome of preterm infants is needed.

### Possible negative effects of giving T4

Thyroxine is infrequently given to extremely premature babies. The only adverse effect that might be predicted is based on clinical experience of giving the drug to more mature patients, namely a persistent tachycardia. The drug may increase metabolic rate. In the critical paper by van Wassanaer et al[8], there was no difference in neurodevelopmental outcome as a result of T4 supplementation. However, a *post hoc *subgroup analysis showed that more mature babies who were given T4 supplementation had a worse neurodevelopmental outcome than those who were unsupplemented. The mechanism for this possible effect is not known.

### Levothyroxine pharmacokinetics

There has been no previous work in this patient group on the circulating blood concentrations of thyroid hormones following the administration of levothyroxine. Establishing whether each infant has similar circulating blood concentrations will be an important aspect of the explanatory RCT. We will use population pharmacokinetic techniques. These will allow us to derive information about circulating thyroid hormone concentrations using measurements done on blood samples taken during routine clinical practice.

In summary, the literature indicates that several areas of uncertainty will hamper randomised controlled studies of interventions for hypothyroidism in extremely preterm infants. These areas include: the optimal timing of monitoring, whether it is appropriate to use reference ranges based on cord blood values, the effect of cortisol status on thyroid function and the relationship between thyroid status and HPA axis. None of these issues can be clarified unless infants who receive thyroid supplementation are prospectively compared to infants who do not receive thyroid supplementation.

In the light of the issues outlined above, an explanatory[49] randomised controlled trial of thyroid supplementation is proposed in infants below 28 weeks' gestation, with an assessment of its effect on short term explanatory outcomes. This study will markedly enhance the design and interpretation of future large-scale studies aimed at determining the effect of such supplementation on long term neurodevelopmental outcome.

There is therefore an urgent need for a larger scale study to discover whether thyroid supplementation benefits these very premature babies. This proposed study will examine the effects of one commonly used form of thyroid supplementation on key intermediate outcomes in these infants. We will also extend previous work in this area by exploring perinatal factors which could modulate the effects of thyroid supplementation

## Aims of the study

To determine how treatment with levothyroxine (LT-4) postnatally until 32 weeks corrected gestational age (CGA) modulates brain size and development, the hypothalamic-pituitary-adrenal axis (HPA) and somatic growth in a randomised double blind placebo-controlled trial.

### Objectives

#### Primary Outcome

• Effect of levothyroxine therapy on brain size as assessed by the width of the subarachnoid space [54] measured at 36 weeks CGA using cranial ultrasound and serial head circumference as an index of brain weight[50,51].

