#### Secondary Outcomes

(a) Serial head circumference as an index of brain weight

(b) Longitudinal thyroid hormone concentrations between birth and expected date of delivery;

(c) Cortisol hormone status between birth and expected date of delivery

(d) Auxological data at pre-randomisation, day 14, day 21, day 28 and at 36 weeks' CGA

(e) Thyroid gland size measured by ultrasound imaging

(f) Mortality

(g) The volumes of key brain structures, whole brain volume, extent of myelination of cerebral white matter and white matter integrity and brain vessel morphology using brain MRI examinations at term equivalent

(h) Duration of mechanical ventilation/oxygen requirement

(i) Chronic lung disease requiring home oxygen at discharge

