### Growth and Auxology

All infants will be measured for weight, lower leg length (using knemometry) and occipito-frontal circumference before commencing treatment (baseline), day 14, day 21, day 28 and at 36 weeks' CGA.

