## Statistical Consideration

### Sample Size Calculation

A sample size of 64 in each group will have 80% power to detect a difference between the means of the thyroxine and placebo groups of 0.67 mm (0.5*SD) for the outcome subarachnoid space at 36 weeks' CGA. This assumes that the common standard deviation is 1.3 mm and analysis is based on using a two group t-test with a 0.05 two-sided significance level. The value for the SD is taken from Armstrong et al[54] who report subarachnoid space as an indirect method of brain growth in preterm infants.

To ensure the appropriateness of the SD used in our calculations we will run an internal pilot after the first 30 infants have been randomised. We will compare the SD of these 30 infants with the standard deviation of Armstrong et al[54]. An internal pilot[49] can be used to increase but not decrease the size of the study. Assuming the 20% loss to follow up that we have experienced in an ongoing trial on the unit, we aim to recruit and randomise 150 infants with gestation below 28 weeks'.

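### Head circumference is part of the primary outcome in the Abstract and Objectives but is listed as a secondary outcome, while the trial is powered on subarachnoid width alone

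*Protocol article*

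**What the plan says.** Four places in the protocol article bear on this.

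- **Abstract, Methods.** The primary outcome, brain growth, is to be "assessed by the width of the sub-arachnoid space measured using cranial ultrasound and head circumference at 36 weeks' corrected gestational" age. Head circumference is primary here, and the natural reading is a single value at 36 weeks.
- **Objectives, Primary Outcome.** The outcome is the effect of levothyroxine on "brain size as assessed by the width of the subarachnoid space [54] measured at 36 weeks CGA using cranial ultrasound and serial head circumference", the last described as an index of brain weight. Head circumference is again primary, but now as a series.
- **Objectives, Secondary Outcomes.** Item (a) is "Serial head circumference as an index of brain weight", the same phrase as in the primary outcome. Item (d) is "Auxological data at pre-randomisation, day 14, day 21, day 28 and at 36 weeks' CGA". The Growth and Auxology section schedules "occipito-frontal circumference before commencing treatment (baseline), day 14, day 21, day 28 and at 36 weeks' CGA", so head circumference appears to fall under (d) as well.
- **Sample Size Calculation.** The difference to be detected is "0.67 mm (0.5*SD) for the outcome subarachnoid space at 36 weeks' CGA". The test is a two-group t-test at two-sided 0.05 with 80% power. No standard deviation, effect size or power is given for head circumference.

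The Analysis section says that a separate statistical analysis plan will be written before the internal pilot, and that the analysis will be blind to allocation.

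**The concern.** Which outcome is primary is a decision for the protocol. Here a reader can cite the document for head circumference as primary, and equally for head circumference as secondary. If the two measures gave different answers, a report could present head circumference in whichever role suited and point to published text in support.

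The design figures also depend on the answer. The 5% significance level and the 80% power were worked out for one test, that of subarachnoid width. If head circumference is also primary, those two figures no longer describe the trial's primary conclusion in full. How far they depart from it depends on how the two results would be read together.

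**Working it through.** **1. Set the statements side by side.**

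| Place | Status of head circumference | Form |
|---|---|---|
| Abstract | primary | at 36 weeks |
| Primary Outcome | primary | serial |
| Secondary Outcomes (a) | secondary | serial |
| Sample Size Calculation | not mentioned | none |

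The second and third rows cannot both be right. The difference between serial and 36-week is minor, because the 36-week value is the last in the series and the Abstract is a summary. The conflict of status is the substance.

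**2. Reproduce the plan's figure.** Inputs from the Sample Size Calculation: 0.5 SD, two-sided 0.05, 80% power, two-group t-test.

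- Normal approximation: n = 2(1.96 + 0.84)²/0.5² ≈ 62.7, so 63 per group.
- Exact t-test: 63.8, so 64 per group. Power at 64 is 80.1%.

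The stated 64 reproduces at 0.5 SD. With the printed millimetres, 0.67/1.3 = 0.515 SD, the power at 64 is 82.5%. On either input the calculation covers subarachnoid width and nothing else.

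**3. Illustrate what follows if both measures are primary.** The document gives neither a success rule nor a correlation, so both are assumed here: correlation r between the two test statistics from 0 to 0.7, and 80% power for head circumference.

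*Either measure at 0.05 counts as success.* The false-positive rate is 1 − P(|Z₁| < 1.96 and |Z₂| < 1.96), with Z₁ and Z₂ bivariate normal.

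- r = 0: 1 − 0.95² = 9.75%
- r = 0.5: 9.1%
- r = 0.7: about 8.3%

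*Both measures must reach 0.05.* Type I error cannot exceed 5%, because each test alone is held at 5%. Joint power is P(Z₁ < 0.842 and Z₂ < 0.842), where 0.842 is the normal quantile for 80%.

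- r = 0: 0.80 × 0.80 = 64.0%
- r = 0.5: 68.7%
- r = 0.7: 71.3%

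The 64% is not a floor. If benefit means a narrower space but a larger head, the correlation in the direction of benefit could be negative, and joint power would then be below 64%. The document does not settle the sign.

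**4. Check the remedy.** With width as the sole primary outcome, the calculation in step 2 applies as it stands, and 64 per group is unchanged.

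**The case against.** The strongest reply is that the intended primary outcome is clear enough. Only subarachnoid width is powered, and the internal pilot is there to check the standard deviation used in that calculation. The trial is explanatory and meant to inform later large trials. On this view head circumference is just a supporting index of the same construct. The inference about intent is reasonable, but the Abstract and the Primary Outcome section join the two measures without ranking them, and a reader should not have to deduce the primary outcome from the sample size paragraph.

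Three stronger readings are tempting, and the document does not support them.

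- *The plan has no rule for combining the two measures or for handling multiplicity.* Such rules commonly sit in the statistical analysis plan, which the article promises and which is not shown. Their absence from a condensed article is not a fault. However, no analysis plan could agree with both outcome lists.
- *The 5% level holds only if width is the sole primary outcome.* This is wrong where both measures must succeed, since type I error then stays at or below 5% and only joint power falls. Nor does naming a second outcome change the 80% power of the width test itself.
- *The choice of primary outcome is left until the data are seen.* The analysis plan is due before the internal pilot, which follows the first 30 randomised infants, and the analysis is blind to allocation. These safeguards limit outcome switching, though they do not repair the wording.

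**Conclusion.** The point stands as an internal contradiction over the status of head circumference: primary in the Abstract and the Primary Outcome section, secondary in item (a) of the Secondary Outcomes, and absent from the sample size calculation. This rests on the text alone and needs no assumption. It should be corrected, because it concerns the outcome by which the trial will be judged.

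The size is conditional. The 8.3% to 9.75% false-positive rate and the 64% to 71% joint power illustrate two hypothetical success rules. They rest on assumed correlations and, for joint power, on an assumed 80% power for head circumference. They are not properties of the plan as written. What the document does support is narrower: its 5% and 80% describe the test of subarachnoid width only.

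**What to change.** Name width of the subarachnoid space at 36 weeks' corrected gestational age as the single primary outcome, since it is the only one powered. This takes two edits, because the two places are worded differently:

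- In the Primary Outcome section, end the definition after the ultrasound measurement and delete the clause on serial head circumference as an index of brain weight.
- In the Abstract, remove head circumference at 36 weeks from the primary outcome.

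Keep serial head circumference as secondary outcome (a). While editing, it would help to say whether auxology in (d) includes it too, so that it is not listed twice.

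The cost is a wording amendment. The sample size stays at 64 per group, and no measurement or visit is dropped. The small downside is that head circumference loses its primary label.
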